### Follow-up

The study is primarily confined to the time period when a woman is in childbirth. Women enter the study from the time that they request opioid pain relief in labour and remain in the study for the duration of labour until both mother and baby have been discharged from hospital.

The period is, therefore, measured in days. Active data collection will only occur up to the point of child birth. There will be a single maternal contact thereafter to administer a brief questionnaire which includes metrics of maternal satisfaction. Mean stay in hospital after spontaneous vaginal delivery is 1–2 days. This period can be extended if delivery by emergency caesarean section has been required.

The trial schema which includes eligibility criteria and outcome measures is shown in Additional file 2: Figure S1.

#### Monitoring of all types of adverse event

All types of adverse event which occur to a woman in the RESPITE trial will be reported as soon as possible after research staff become aware of the event. A Serious Adverse Event Form should be completed as fully as possible and sent via fax or email (from an NHS account) to the Trials Office. This form will include an assessment of causality. Upon receipt, the Trials Office will log details of the adverse event on that patient’s record on the central trials database and forward an anonymised copy of the form to the chief investigator.

Anonymised details of all adverse events will be presented to the Data Monitoring Committee (DMC) for scrutiny each time they meet. These anonymised details will be reported to the Research Ethics Committee (REC) and Medicines and Healthcare Products Regulatory Authority (MHRA) annually.

### Statistical analysis

#### Sample size

Epidural conversion rates of approximately 10% (range 5% to 19%) are commonly reported after remifentanil. This compares to conversion rates of greater than 30% (range 17% to 39%) being representative in women receiving pethidine. Taking a deliberately conservative estimate of intervention effect using these data, a reduction in epidural conversion from 30% (pethidine) to 15% (remifentanil PCA) is reasonable. To detect such a reduction with 90% power at *p* = 0.05, would require 161 women in each arm of the trial, yielding a sample size of 322 in total. Adjustment must also be made to account for attrition of the study population as labour progresses. A proportion of the women will require urgent delivery, by caesarean section, for foetal indications before a request for further analgesia can be made. Assuming that this will not represent more than 25% of the sample after randomisation (reflecting the national caesarean section rate) and a 15% emergency caesarean rate is more realistic, a further 48 women will be recruited to offset this attrition of participants who are not capable of reaching the primary outcome. Allowing for a modest unavailability of primary outcome data and nonadherence of 6%, a total sample size of 400 is, therefore, proposed.

A detailed analysis plan will be developed and agreed by the TSC and the DMEC. Demographic factors and clinical characteristics will be summarised with counts (percentages) for categorical variables, mean (standard deviation) for normally distributed continuous variables, or median (interquartile or entire range) for other continuous variables.

#### Primary analysis

The primary analysis will be a comparison of the management policies assigned at randomisation (intention-to-treat population.) The risk of the primary outcome in the remifentanil PCA group will be compared with the group and tested for significance at the two-sided 5% level of significance. In addition to the primary unadjusted analysis, a log-binomial model will be used to account for the minimisation variables. Risk ratios and 95% confidence intervals will be estimated. As the remifentanil PCA will generally only be available within the context of the RESPITE trial, we do not anticipate many protocol deviations; however, a limited incidence of nonadherence is predicted. The most likely cause is rapidly progressing labour with delivery occurring after randomisation, before allocated pain relief can be administered.

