### Randomisation

Randomisation will be carried out via a web-based central service (with staffed telephone back-up during office hours) based at Birmingham Clinical Trials Unit (BCTU). A 24-h, 7-day, interactive, telephone-based randomisation service will also be provided by the Health Services Research Unit at the University of Aberdeen. The web-based central service is only available to those named on the delegation log, whereas both telephone services are also available to clinical midwives, nurses and operating department practitioners (ODPs).

To obtain a randomised allocation and trial number, the person performing the randomisation process will need to verify a woman’s date of birth, confirm that all eligibility criteria have been met and provide the minimisation variables. At randomisation a confirmatory email will be sent to the randomising investigator, the local principal investigator (PI) and the research midwife/nurse. A ‘minimisation’ procedure using a computer-based algorithm will be used to avoid chance imbalances in parity, an important prognostic variable, which will be considered as an ordinal variable.

Minimisation variables will be:Parity: nulliparous versus multiparousMaternal age: <20, 20 < 30, 30 < 40, 40+ years.Ethnicity: South Asian (Pakistani/Indian/Bangladeshi) versus OtherInduced versus spontaneous labour

The procedures for randomisation will be fully documented and tested prior to the start of the trial and monitored by BCTU.

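### The primary comparison is unadjusted although allocation is minimised on four factors; if those factors are prognostic the test is mildly conservative, and the adjusted analysis should be primary

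*Protocol article*

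**What the plan says.** The Randomisation section of the protocol article lists four minimisation variables: parity (two levels), maternal age (four levels), ethnicity (two levels) and induced versus spontaneous labour. It gives the purpose as "to avoid chance imbalances in parity, an important prognostic variable". The Subgroup analysis section adds that previous labours may influence the request for an epidural, which is the primary outcome.

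The Primary analysis section compares the arms by intention to treat, "tested for significance at the two-sided 5% level of significance". It then orders the two analyses: "In addition to the primary unadjusted analysis, a log-binomial model will be used to account for the minimisation variables". It continues: "Risk ratios and 95% confidence intervals will be estimated".

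The Sample size section leaves further detail to a separate analysis plan, which is not shown. The order of the two analyses and the type of model are nevertheless fixed in the article itself.

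**The concern.** Minimisation forces the arms to be alike on the chosen factors. If a factor predicts the outcome, the difference between arms then varies less from trial to trial than under simple randomisation. An unadjusted test uses a variance that assumes simple randomisation, so its standard error is too large and its true type I error falls below the nominal 5%. Adjusting for the factors brings the standard error back into line with the allocation.

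The protocol itself says that one of the four factors is prognostic, yet it gives the deciding role to the analysis that does not use it. At stake are a somewhat wide confidence interval, a small loss of power if the true effect is smaller than planned, and a less suitable governing result if the two analyses fall on opposite sides of 5%.

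The log-binomial model raises a smaller question. Its log link does not keep fitted risks below 1, so the fit can stop on the boundary or fail to converge.

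**Working it through.** **1. The plan's own figure.** The protocol states that "a reduction in epidural conversion from 30% (pethidine) to 15% (remifentanil PCA) is reasonable" and that this "would require 161 women in each arm of the trial, yielding a sample size of 322 in total", with 90% power. Use the pooled-variance formula for two proportions without continuity correction:

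n = [z(0.975)·√(2p̄q̄) + z(0.90)·√(p₁q₁ + p₂q₂)]² / (p₁ − p₂)²

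With p₁ = 0.30, p₂ = 0.15 and p̄ = 0.225:

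n = [1.96 × √0.34875 + 1.2816 × √0.3375]² / 0.0225 = (1.1575 + 0.7445)² / 0.0225 = 160.8, so 161 per arm.

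This matches. The inflation also holds: 322 × 0.15 = 48.3; 322 + 48 = 370; 370 / 0.94 = 394, close to 400. The figure of 161 is for an unadjusted comparison, so the sample size does not depend on this point.

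**2. Inputs for the simulations.** From the protocol: 400 women, 1:1 allocation, four minimisation factors with their levels, two-sided 5%, 30% v 15%. The protocol does not give case mix, prognostic strength or the minimisation probability, so these are assumed:

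| | Simulation A | Simulation B |
|---|---|---|
| Nulliparous | 60% | 60% |
| Induced | 45% | 40% |
| Age <20 / 20s / 30s / 40+ | 5/50/41/4% | 5/50/42/3% |
| Probability of the balancing arm | 0.85 | 0.80 |
| Odds ratios (parity, induction) | 2, 1.5; 3, 2; 5, 2.5 | none; 2.5, 1.6; 5, 2.5 |
| Null event rate | 30% | 30% |

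Simulation B also assumed 15% South Asian. The adjusted test is modified Poisson regression with robust variance.

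**3. Type I error.**

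| Prognostic strength | Unadjusted | Adjusted |
|---|---|---|
| A: OR 2, 1.5 | 5.2% | 5.6% |
| A: OR 3, 2 | 4.3% | 5.1% |
| A: OR 5, 2.5 | 3.9% | 5.2% |
| B: none | 5.1% | 4.9% |
| B: OR 2.5, 1.6 | 4.7% | 6.2% |
| B: OR 5, 2.5 | 3.6% | 4.6% |

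The Monte Carlo standard error is √(0.05 × 0.95 / 5,000) = 0.3 points in A. In B it is √(0.05 × 0.95 / 7,000) = 0.26 points for the unadjusted test and √(0.05 × 0.95 / 1,500) = 0.56 points for the adjusted test.

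**4. Cross-check.** The largest overstatement of the standard error in A was 0.154 / 0.147 = 1.048. A nominal 5% test with that overstatement has true size 2 × [1 − Φ(1.96 × 1.048)] = 2 × [1 − Φ(2.05)] ≈ 4.0%. This agrees with the simulated 3.9%.

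**5. Power.** At 30% v 15% with 200 per arm, the normal approximation for the unadjusted test is Φ[(0.15 − 1.96 × √(0.34875/200)) / √(0.3375/200)] = Φ(0.0682 / 0.0411) = Φ(1.66) ≈ 95%. Simulation B gave about 95% to 97% for both tests. Simulation A, at a risk ratio of 0.5 from a 24% control rate, gave a change of −0.4 to +0.8 point on adjusting.

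At an assumed 30% v 18% (simulation B):

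| Prognostic strength | Unadjusted | Adjusted | Gain |
|---|---|---|---|
| None | 80.8% | 81.8% | 1.0 |
| OR 2.5, 1.6 | 82.1% | 83.4% | 1.3 |
| OR 5, 2.5 | 82.6% | 85.9% | 3.3 |

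The adjusted figures come from 1,500 runs, with a Monte Carlo standard error of about 1 point (√(0.82 × 0.18 / 1,500) = 0.0099). Only the last gain is clearly beyond noise.

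**6. Log-binomial fit.** The model has 1 treatment + 1 parity + 3 age + 1 ethnicity + 1 induction = 7 coefficients plus an intercept. Expected events at 30% v 15% are 200 × 0.30 + 200 × 0.15 = 90. In simulation B, default iteratively reweighted least squares failed or gave an invalid fit in 4%, 19% and 47% of trials as prognostic strength rose. With step-halving, 1.6%, 12.6% and 32.2% stayed unconverged or on the boundary (500 runs each). Simulation A, with a default fitter, gave 15% (OR 3, 2) and 28% (OR 5, 2.5).

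**The case against.** The strongest reply is that little turns on this. The error is in the safe direction, the standard error is overstated by at most about 5% in the scenarios tried, power at the planned effect is the same for either test, and the unadjusted test is the one the trial was sized for. All of that stands. It limits the size of the point but does not remove it, because the better analysis uses variables that are already collected.

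It is also fair that the adjusted test is not exact. Two of its six simulated type I errors (5.6% and 6.2%) lie about two Monte Carlo standard errors above 5%. The six average (5.6 + 5.1 + 5.2 + 4.9 + 6.2 + 4.6) / 6 = 5.3%, so a slight excess cannot be ruled out, but no consistent inflation is shown.

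Three stronger readings are tempting, and the document does not support them:

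- *The plan ignores the minimisation factors.* It does not: an adjusted analysis is prespecified beside the primary one. The issue is only which of the two leads.
- *The log-binomial model often fails.* Failure was rare when the factors had no effect and frequent only when they were strong. The protocol gives no effect sizes, and part of the failure comes from the fitting routine.
- *The adjusted risk ratio may be unobtainable, or force an unplanned change of model.* A fallback commonly sits in the analysis plan, which is not shown, so its absence from the article is no finding. A failed adjusted model would also leave the unadjusted primary risk ratio intact.

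**Conclusion.** The point holds in a limited form. The protocol fixes an unadjusted primary test after minimising on four factors, one of which it calls prognostic. If the factors matter, that test is mildly conservative: type I error is about 5% with no or weak effects and 3.6% to 3.9% with parity and induction odds ratios of 5 and 2.5. There is no risk of excess false positives, no consequence for the sample size and almost none for power at 30% v 15%. The gain from adjusting, about 1 to 3 points, appears at an assumed 30% v 18%.

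The direction follows from the design and was seen in both simulations. The size rests entirely on assumed case mix, odds ratios and minimisation probability. The choice of log-binomial model is a secondary weakness: the risk of a failed fit is real, and it is greatest when the factors are strong, which is when adjustment is worth most.

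**What to change.** In the Primary analysis section, and in the analysis plan, name the analysis adjusted for parity, age group, ethnicity and induction as primary and the unadjusted comparison as supportive. Enter parity in the two levels used for minimisation; the Randomisation section also describes it as ordinal, so the coding should be stated.

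Estimate the adjusted risk ratio and its 95% confidence interval by modified Poisson regression with robust variance, or by logistic regression with marginal standardisation. Neither depends on the log-binomial model converging.

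The cost is wording only. All four variables are recorded at randomisation, and the sample size stays as it is. The Trial status section says that recruitment is still open, so the change can be made and dated before the results are known.

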#### Subgroup analysis

Perception of pain during labour may be influenced by previous experiences, in particular previous labours, and this may, in turn, influence the request for epidural. Maternal parity will, therefore, be prespecified for subgroup analysis of primary outcome.

#### Handling missing data

The extent of missing data for the primary outcome should be limited, as it is routinely recorded in maternity records and can be collected retrospectively. The Maternal Outcome Satisfaction Questionnaire must be completed before discharge and research nurses/midwives should make every effort to collect this. Where these time-critical data are missing, multiple imputation methods may be considered to inform a sensitivity analysis.

### Data management and quality assurance

#### Data form confidentiality

Personal data and sensitive information required for the RESPITE trial will be collected directly from trial participants and hospital notes on paper Data Collection Forms, coded with the woman’s unique trial number and initials. Women will be informed about the transfer of this information to the RESPITE trial office at BCTU and asked for their consent. All personal information received in paper format for the trial will be held securely and treated as strictly confidential according to BCTU policies. All staff involved in the RESPITE trial share the same duty of care to prevent unauthorised disclosure of personal information. No data that could be used to identify an individual will be published.

#### Confidentiality of RESPITE database

RESPITE data will be electronically stored and managed on a dedicated, secure, encrypted trial database, specifically constructed for the purpose. The data will be entered onto a secure computer database, either directly via the Internet using secure socket layer encryption technology or indirectly from paper by BCTU staff. The RESPITE database at BCTU is managed under the provisions of the Data Protection Act and/or applicable laws and regulations.

Randomisation can be achieved either via the web-based randomisation module of the trial database, or by use of a touch-tone activated telephone system, via the University of Aberdeen, which synchronises with the RESPITE database.

Access to the randomisation module and data entry screens of the database will be controlled via individual username and passwords assigned to research midwives/nurses and physicians identified on the delegation log as having responsibility for data collection, and by BCTU trial staff. Transcription of paper forms on to the RESPITE database will be performed either at the site, or the paper form will be faxed to BCTU.

#### In-house data quality assurance and validation

The study will adopt a centralised approach to monitoring data quality and compliance. A computer database will be constructed specifically for the study data and will include range and logic checks to prevent erroneous data entry. Independent checking of data entry of paper questionnaires will be periodically undertaken on small subsamples. The trial statistician will regularly check the balance of allocations by the minimisation variables. Source data verification will only be employed if there is reason to believe that data quality has been compromised, and then only in a subset of practices.

#### Long-term storage of data

In line with the impending revision of the Medicines for Human Use (Clinical Trials) Regulations, once data collection is complete on all participants, all data will be stored for at least 25 years. This will allow adequate time for review and reappraisal, and in particular with the RESPITE trial, form the basis for further follow-up research. Any queries or concerns about the data, conduct or conclusions of the trial can also be resolved in this time. Limited data on the participants and records of any adverse events may be kept for longer if recommended by an independent advisory board.

Trial data will be stored within BCTU under controlled conditions for at least 3 years after closure. Long-term offsite data-archiving facilities will be considered for storage after this time. BCTU has standard processes for both hard copy and computer database legacy archiving.

## Discussion

This protocol describes the RESPITE randomised controlled trial, which will evaluate the effectiveness of remifentanil intravenously administered PCA compared with pethidine im injection (the current, standard opioid analgesic for women in established labour). This will be assessed by comparing epidural conversion rates in each study arm. This multicentre study will recruit 400 women in childbirth and the results will be used to make recommendations on the subsequent adoption of remifentanil into clinical practice in childbirth via publications and clinical guidelines.

Many UK units now routinely offer remifentanil PCA in cases where an epidural is contraindicated and a very restricted number make it available ‘on demand’ as an alternative analgesic intervention in labour. Those units which have pursued adoption into routine practice have now accumulated the experience of the safe administration of remifentanil PCA to several thousand women in childbirth. However, the summary of product characteristics for remifentanil states that there are insufficient data to recommend its use in labour or caesarean section, so in effect this usage is off label. The challenges of conducting clinical trials of investigational medicinal products (CTIMPs) to the standard of GCP required by regulatory authorities are well-known [24].

For RESPITE, the use of remifentanil outside its licenced indication places the trial in a higher-risk category according to the guidance of the MHRA [25]. This does not necessarily reflect an increased risk to the trial participants but an acknowledged lack of data. However, it increases the burden of risk management and monitoring on those conducting the trial.

Another challenge for RESPITE is the intrapartum recruitment of women in active labour. We have adopted the recommendation of the RCOG, in which the timing and extent of the information provided to women is adapted according to the risk of becoming eligible for the trial [26]. A considerable proportion of women require analgesia, so we ensured that all women booked to deliver at participating hospitals receive information about the study at the antenatal clinic, during their pregnancy and again on admission in labour. The majority of the eligibility criteria can be determined on admission in labour. To avoid a situation where consent is sought from a woman in pain and distress, consent to participate can be sought from the point that labour is considered to be established, or is induced, up to and including the point when the final eligibility criteria, that of requesting opioid analgesia, is apparent. This allows the research midwife to fully discuss the trial and gain valid consent from a woman who is considering participation, and also prepare the eligibility checklist to enable a delivery suite midwife to complete the final step of randomisation if, and when, the request for opioids is made by the woman. Randomisation may, therefore, continue even if the research midwife is not present, essential in intrapartum situations. It is widely accepted that suitably trained research nurses and midwives are appropriate persons to seek consent for participation in a clinical trial [27]. Under the principles of GCP, the decision as to whether a patient is eligible for entry into a trial is considered to be a medical decision and, therefore, must be made by a medically qualified doctor. In the RESPITE study, this decision can be made by an anaesthetist or obstetrician, but it is acknowledged that physicians are not routinely present when a woman requests opioid analgesia. Indeed, pethidine, although a controlled drug in UK law, can be independently prescribed by a qualified midwife. MHRA acknowledges that there are certain situations where the assessment of eligibility can be broadened to include professionals who are not medically qualified, such as midwives or nurses. This provision is subject to the following criteria:The role of nonmedical professionals in determining eligibility has been risk-assessedThe role of nonmedical professionals is consistent with standard clinical practice and that arrangements for the clinical trial should not fall below that standardThe duties involved in determining eligibility have been delegated by an appropriately trained and qualified member of site staffThe eligibility assessment process should be overseen by a medically qualified doctor

It is imperative that the roles and responsibilities are clarified and communicated with the regulatory authorities prior to the start of any trial facing similar challenges. This exemption is essential for intrapartum research and other situations where nonmedical health care professionals with advanced prescribing responsibilities are the primary care providers.

### Trial status

RESPITE is currently recruiting.

## Abbreviations

BCTU: Birmingham Clinical Trials Unit
CTIMP: Clinical Trial of an Investigational Medicinal Product
DMC: Data Monitoring Committee
DMEC: Date Monitoring and Ethics Committee
GCP: Good Clinical Practice
IM: Intramuscular
ISRCTN: International Standard Randomised Controlled Trial Number
MHRA: Medicines and Healthcare Products Regulatory Authority
NHS: National Health Service
NIHR: National Institute for Health Research
NRES: National Research Ethics Service
ODP: Operating department practitioner
PCA: Patient-controlled analgesia
PI: Principal investigator
PPI: Patient and Public Involvement
PRIME: Public and Researchers Involvement in Maternity and Early pregnancy group
RCOG: Royal College of Obstetricians and Gynaecologists
REC: Research Ethics Committee
ScHARR: School of Health and Related Research
TMG: Trial Management Group
TSC: Trial Steering Committee
